**trial PROTOCOL**

**Title**

Early identification of warfarin maintenance dose

Warfarin, the most prescribed oral anticoagulant, in Italy, in the year 2008 approximately 6,500,000 subjects were estimated to be on warfarin, the annual increase being 5%. Warfarin has a very narrow therapeutic window and wide and unpredictable inter-individual variability in dose-response leading to a difficult achievement and control of its antithrombotic effect.

This orally administered drug is a racemic mixture of S- and R-warfarin that differ in terms of their pharmacokinetic and pharmacodynamic properties. S-warfarin is by far more pharmacologically active than R-warfarin, is largely absorbed (>90%) after oral administration and is inactivated in the liver by cytochrome CYP2C9. The activity of this enzyme is extremely variable in the population mainly due to the presence of 2 allelic variants (CYP2C9*2 and CYP2C9*3) associated with reduced activity compared to the common wild-type allele (CYP2C9*1). The combination of these 3 main alleles gives rise to 6 different genotypes associated with a decreasing enzymatic activity: *1*1>*1*2>*1*3>*2*2>*2*3>*3*3 [1]. Moreover many pharmacological interactions have been reported resulting either in the induction or inhibition of cytochrome P450 2C9 itself.

Similarly complex is the relation between concentration of the drug and its effect since the gene encoding for the target of warfarin – Vitamin K epoxide reductase- is also polymorphic and certain genetic variants (VKORC1 1173 C>T and -1639G>A in complete linkage [2]) have been demonstrated to been associated with reduced warfarin requirements [3]. Since warfarin competes with vitamin K for the binding to vitamin K epoxide reductase, the food intake of vitamin K is an important factor modulating the anticoagulant effect.

A further aspect of these complex phenomena is the lag time between drug administration and the onset of the antithrombotic activity which depends on the progressive decrease of the vitamin K dependent coagulation factors (II, VII, IX and X).

Moreover a recent study demonstrated that a genetic polymorphism (rs2108622; V433M) in cytochrome P450 4F2 (CYP4F2) was associated with warfarin dose [4] .

Currently warfarin maintenance dose is individually adjusted after a standard initial dosing on the basis of the international normalized ratio (INR) monitoring protocols (trial and error schemes). During the initial phase of the treatment, often lasting weeks or even months, patients may be at risk of thrombotic (drug under-dosing) and bleeding (drug over-dosing) events. The scheme for warfarin treatment validated [5] and currently adopted by our Institution is based on the consecutive administration of a 5 mg warfarin dose the first 4 days and the INR measurement at day 5. On the basis of the hyperbolic correlation existing between day 5 INR and warfarin maintenance dose it is possible to calculate the weekly warfarin dose of the drug (Table 1).

The attending physician prescribes subsequent adjustment in warfarin dosing with the assistance of the PARMA v5.7 software [6].

During the last years several research groups [4, 7-10] have tried to determine which demographic (age, sex, weight, height, etc.) and genetic factors (VKORC1, CYP2C9 and CYP4F2)associated with warfarin maintenance dose might be useful in predicting initial drug dosing. These studies demonstrated that the pharmacogenetic approach can predict 50% of the inter-individual variability if warfarin dosing.Our Group has recently developed, in a retrospective study, a pharmacogenetic algorithm, based on patients’ age and body surface area (BSA) and *VKORC1*, *CYP2C9*, *CYP4F2* polymorphisms. This algorithm could explain 55% of warfarin dose variability and allowed the correct prediction of warfarin dose regimens in the great majority of the Italian patients. VKORC1 genotype information can also be used to predict the personalized loading dose of warfarin in order to achieve more rapidly the optimal anticoagulation (INR 2.5).

The study is aimed to verify if patients with atrial fibrillation may benefit in term of anticoagulation control and safety from the advanced prediction of their personalized warfarin loading and maintenance dosage with respect to patients treated according to the standard care (a posteriori adjustment) adopted in our Institution.

**STUDY DESIGN:**

The study will enroll warfarin-naïve patients with atrial fibrillation and indication for warfarin treatment with target INR between 2.0 and 3.0.

Patients will be randomized to receive initial warfarin doses either established according to the standard care (control group) or determined by the pharmacogenetic algorithm (intervention group) according to individual age, BSA and *CYP2C9, CYP4F2*and*VKORC1* genotypes.

Patients will be selected based on the following eligibility criteria:

Inclusion criteria:

- Age >18 years
- Non-valvular atrial fibrillation
- Warfarin-naïve patients with indication for warfarin treatment with target INR between 2.0 and 3.0

Exclusion Criteria:

- Pregnancy (present or planned)
- Treatment with drugs interfering with warfarin (Amiodarone, rifampin and carbamazepine)
- Basal INR > 1.2
- Unwillingness to sign an informed consent statement.

Primary outcome measuresof the study are:

- percentage of INR out of range (INR<2 or>3) of each patient[ Time Frame: Day 0-19 ];
- time in therapeutic range (TTR) defined as the fraction of the study time (days) spent within the therapeutic range (INR 2-3) by patients belonging to the two arms [11][Time Frame: Day 0-19 ];

Secondary outcome measures of the study are:

- number of changes in warfarin dosage [ Time Frame: Day 0-19 ] ;
- difference between predicted and actual warfarin maintenance dose [ Time Frame: Day 19 ];
- thromboembolic and Bleeding complications [ Time Frame: Day 0-30 ].

**STUDY PROCEDURES**

Patients enrollment will be performed from Monday to Wednesday at the Anticoagulation Clinic of the University Hospital of Padova. Fully informed consent will be obtained in writing from all the participants.

The day of enrolment clinical data will be recorded and 15mL of peripheral blood will be collected (for routine testing and genetic analyses). Patients accepting to participate in the study will be randomly assigned to control group or intervention group. The assignment to the study groups will be performed by block randomization . On Wednesday genetic analyses of rs9923231 (*VKORC1* -1639G>A), rs1799853 and rs1057910 (*CYP2C9 *1*, **2* and **3* alleles) and of rs2108622 (*CYP4F2 *1* and **3* alleles) will be performed for each patients at the Department of Laboratory Medicine of the University Hospital of Padova by means of Real Time PCR. Results will be available within Thursday morning in order to calculate the predicted warfarin maintenance dose of patients in the intervention group by means of the pharmacogenetic algorithm. From the day of enrolment till the initiation of treatment patients will be prescribed Enoxaparin (4000 IU q.d. subcutaneously).On Thursday patients of both arms will start treatment (day 1). During the observational period of the study, which encompasses the first 19 days of the treatment, patients will be examined at the Anticoagulation Clinic of the University Hospital of Padova at day 5, 7, 9, 12, 15, 19. At each time point INR will be measured to monitor the intensity and control of anticoagulation. The study flow chart is reported in figure 1.

Control Group (control arm)

Patients treated according to standard care will be administered 5mg warfarin at 8 p.m. for 4 consecutive days (day 1 to day 4 ) and INR value detected at day 5 (Monday, INR1) will be used to establish the warfarin dosing according to table 1. Five following visit will be scheduled for each patient at day 7 (Wednesday, INR 3), 9 (Friday, INR 5) of the first week of treatment, at day 12 (Monday INR 8), 15 (Thursday, INR 11) of the second week of treatment and finally at day 19 (Monday, INR 15) of the third week of treatment. Each patients will receive a timetable of the scheduled follow-up. The attending physician will be allowed to perform further visits on the basis of safety considerations. At each visit a peripheral blood sample will be collected from patients for INR measurement.

Intervention group (PGX Arm)

Patients treated according to the pharmacogenetic scheme will be administered, at 8 p.m., in the first four days of treatment (day 1 to day 4) warfarin dosage will be calculated on the basis of pharmacogenetic results. The first day each patients will be administered a loading dose calculated on the basis of his weight and VKORC1 genotype according to the following scheme:

| genotype | Loading dose (mg) |
| --- | --- |
| VKORC1 AA | 0.25 ×weight× 0.14 |
| VKORC1 GA | 0.34 ×weight× 0.14 |
| VKORC1 GG | 0.52 ×weight× 0.14 |

This table is derived from the formula for the one-compartment pharmacokinetic model:

Loading Dose (LD) (mg) = volume of distribution (L) × target steady state plasma concentration (mg/L).

The volume of distribution will be estimated on the basis of body weight (0.14 L/Kg) [12], while the target steady state plasma concentration (mg/L) will be calculated according to a pharmacokinetic-pharmacodynamic model described by Hamberg and colleagues [13]

a) 0.25 mg/mL for *VKORC1 AA*;

b) 0.34 mg/mL for *VKORC1 GA*;

c) 0.52 mg/mL for *VKORC1 GG*.

In any case the maximum loading dose to be administered will not be higher than 10mg for safety reason.

From day 2 till day 6 of treatment warfarin dosages will be calculated on the basis of age , Body Surface Area (BSA) and CYP2C9, CYP4F2 and VKORC1 according to the following pharmacogenetic algorithm:

Dose di mantenimento = [7.40 – 0.027(age) + 1.06(BSA) – 1.04(VKORC1 AG) – 2.12(VKORC1)AA) – 0.79(CYP2C9 *1*2) – 1.17(CYP2C9 *1*3)

– 1.81(CYP2C9 *2*2+*2*3+*3*3) – 0.71(CYP4F2 CC) – 0.47(CYP4F2 CT)]**^0.5^**

From day 7 of treatment (Wednesday, INR 3) onward the attending physician on the basis of INR results and his clinical experience will adjust warfarin dosage according to standard care as in the control group of patients. Each patients will receive a timetable of the scheduled follow-up. The attending physician will be allowed to performed further visits on the basis of safety considerations. At each visit a peripheral blood sample will be collected from patients for INR measurement.

Statistical analysis

Statistical analysis will be specified and planned prior to any comparative analysis. We exclude an on-going interim analysis.

For both primary and secondary endpoints, it is considered appropriate to test the null hypothesis by a two side α levels.

Before proceeding with inferential analyses, the data will be fully inspected by an exploratory analysis. Descriptive statistics will be used to inspect data; categorical data will be expressed as frequencies and the 95% confidence intervals will be calculated by the exact binomial methods. For continuous data, normality will be at priori assessed by Shapiro Wilk test and by using Q-Q plots. Therefore, mean and standard deviation or medians and ranges will be alternatively used to summary results of continuous data. Differences in potentially clinical covariates (e.g., Age, gender, BMI, BSA, etc.) will be assessed by Student’s t-test (for continuous data) or by Fisher exact test (for frequencies comparison).

For the primary and secondary endpoints, the differences between arms will be assessed by appropriate statistics, according to data distribution.

Sample size calculation

Bases on data from the Thrombosis Center local database, we expect that, during the study period, patients in control arm will experience a percentage of INR measures outside the therapeutic range will be 50%. In order to demonstrate a 10% of improvement in the percentage of INR out of range for the Pharmacogenetic over the Control arm, with a 80% of power, at a 5% significance level, a 23% standard deviation and a drop-out rate of 15%, 100 patients per group will be needed for each arm.

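### The PGX maintenance-dose formula cannot be right as printed: power 0.5 and no unit give doses that are too low and too flat for days 2–6

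*Protocol*

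**What the plan says.** In the Protocol, Study procedures, Intervention group (PGX Arm), day 1 is a weight- and VKORC1-based loading dose. After that, "From day 2 till day 6 of treatment warfarin dosages will be calculated" from a regression on age, BSA and three genes. The formula opens "Dose di mantenimento = [7.40 – 0.027(age) + 1.06(BSA) – 1.04(VKORC1 AG) – 2.12(VKORC1)AA", continues with CYP2C9 and CYP4F2 terms, and closes "0.47(CYP4F2 CT)]^0.5". The power 0.5 therefore applies to the whole bracket. No unit or time base is given, and there is no worked dose. From day 7 the physician adjusts by INR.

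Other parts of the protocol give a scale for comparison:
- Control patients are "administered 5mg warfarin at 8 p.m. for 4 consecutive days", then dosed from Table 1, which runs from 7 to 71 mg/week.
- The target concentrations behind the loading dose are 0.25, 0.34 and 0.52 for VKORC1 AA, GA and GG.
- INR is scheduled "at day 5, 7, 9, 12, 15, 19".
- A secondary outcome is the "difference between predicted and actual warfarin maintenance dose" at day 19.

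**The concern.** This one line defines the experimental treatment for five days, so it has to yield usable doses. A square root of a bracket worth roughly 2 to 9 lies between about 1.4 and 3, which fits neither the weekly nor the daily dose scale used elsewhere in the protocol. It also compresses the differences between genotypes that the trial is meant to exploit.

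The protocol's introduction links under-dosing to thrombotic risk, and enoxaparin is prescribed only until warfarin starts. A misprinted formula that was actually used would therefore be a safety matter. It could also bias the percentage of INR out of range and TTR against PGX, and it would distort the predicted dose in the secondary outcome.

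**Working it through.** The protocol states no dose from the formula, so there is no printed figure to reproduce. The check evaluates the formula directly.

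**Inputs.** Coefficients are from the PGX Arm text: constant 7.40; age −0.027 per year; BSA +1.06 per m²; VKORC1 AG −1.04, AA −2.12; CYP2C9 \*1\*2 −0.79, \*1\*3 −1.17, two variant alleles −1.81; CYP4F2 CC −0.71, CT −0.47. That makes 3 × 4 × 3 = 36 genotype combinations. Ages and BSA values are assumptions. B denotes the bracket.

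**Range of the printed formula.**
- 40 y, 2.2 m², highest genotype: B = 7.40 − 1.08 + 2.332 = 8.652. √B = 2.94; ×7 = 20.6; 2.94/5 = 59%.
- 85 y, 1.5 m², lowest genotype: B = 7.40 − 2.295 + 1.59 − 2.12 − 1.81 − 0.71 = 2.055. √B = 1.43; ×7 = 10.0.
- 19 y, 2.5 m², highest genotype: B = 7.40 − 0.513 + 2.65 = 9.537. √B = 3.09; ×7 = 21.6.

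As mg/week, all values fall below Table 1's minimum of 7. As mg/day, the ceiling of 21.6 mg/week lies below the calculated weekly dose in every Table 1 row for day-5 INR 1.0 to 2.3 (71 down to 22 mg/week), which is 14 of 35 rows.

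**Alternatives at 70 y, 1.8 m².** Before genotype terms, B = 7.40 − 1.89 + 1.908 = 7.418. Over the 36 combinations B runs from 2.778 to 7.418.

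| Reading | mg/week over 36 combinations |
| --- | --- |
| √B as mg/day, ×7 (printed) | 11.7–19.1 |
| B as mg/day, ×7 | 19.4–51.9 |
| B² as mg/week | 7.7–55.0 |

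**By VKORC1 genotype**, same profile, CYP2C9 \*1\*1, CYP4F2 CC:

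| | GG | AG | AA | GG:AA |
| --- | --- | --- | --- | --- |
| B | 6.708 | 5.668 | 4.588 | 1.46 |
| √B, mg/day | 2.59 | 2.38 | 2.14 | 1.21 |
| B², mg/week | 45.0 | 32.1 | 21.0 | 2.14 |
| B²/7, mg/day | 6.43 | 4.59 | 3.01 | 2.14 |
| Printed ÷ squared | 40% | 52% | 71% | |

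The protocol's own target concentrations give GG:AA = 0.52/0.25 = 2.08. The lettered list prints them as "c) 0.52 mg/mL for *VKORC1 GG" although the loading formula uses mg/L, but the ratio does not depend on the unit.

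**Direction of the error.** 7√B is below B² when B exceeds 7^(2/3) = 3.66. That holds for 31 of 36 combinations at 70 y/1.8 m², 36 of 36 at 40 y/2.2 m² and 26 of 36 at 85 y/1.5 m². The five exceptions at 70 y/1.8 m² are all VKORC1 AA with \*1\*3 or two CYP2C9 variant alleles. They come out equal or higher as printed, up to 11.7 against 7.7 mg/week. These counts are not weighted by genotype frequency, which the protocol does not give.

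**Reach into the primary outcome.** There are six scheduled INRs, and those on days 5 and 7 precede any scheduled INR-based PGX adjustment. One extra out-of-range value moves a patient by 1/6 = 16.7 points. The planned difference of 10 points is between group means, so a fraction f of PGX patients with one extra failure shifts the PGX mean by 16.7 × f. Erasing 10 points would need f = 10/16.7 = 60%.

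**The case against.** **Loading dose.** The strongest objection comes from the same section. At an assumed 70 kg the loading table gives 0.52 × 70 × 0.14 = 5.10 mg (GG), 3.33 mg (GA) and 2.45 mg (AA). The squared formula gives 6.43, 4.59 and 3.01 mg/day, so maintenance would exceed the loading dose in all three genotypes. Exponent 1 does the same. Only the printed formula read as mg/day keeps loading above maintenance here. This stands as a warning that exponent 2 is unproven and that the loading table should be checked as well. It does not explain a formula unable to predict any dose above about 21.6 mg/week when the clinic's own table goes to 71.

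**Ratio evidence.** It is mixed. AG:AA is 1.53 squared and 1.24 with exponent 1, against 0.34/0.25 = 1.36, which favours exponent 1. GG:AG is 1.40 and 1.18, against 0.52/0.34 = 1.53, which favours squaring. The ratios are supporting evidence only.

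**Table 1 range.** Read as mg/day, the printed values of 10.0–20.6 mg/week do lie within 7–71. Squaring leaves that range at extreme profiles (4.2 and 74.9 mg/week). The valid objection to the printed line is its low ceiling.

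**Impact.** Day 5 precedes INR-based adjustment in the control arm too, so only day 7 is a disadvantage specific to PGX. In Table 1, a control patient whose maintenance dose is 35 mg/week has a day-5 INR of 1.5, already out of range, so lower PGX dosing need not add a failure that day. Extra safety visits are allowed and could soften the effect. The size of the bias therefore cannot be computed from the document.

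**Conclusion.** The formula is wrong as written, with high confidence: no unit is stated, and neither a weekly nor a daily reading gives a usable set of doses. This rests on the printed coefficients, the assumed age and BSA ranges, and Table 1 as the clinic's own dose scale. Nothing else in the protocol corrects the exponent or supplies the unit.

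That the exponent was inverted (0.5 for 2, in mg/week) is the likeliest explanation but remains an inference. Exponent 1 in mg/day cannot be excluded from the document. If exponent 2 is right, a typical \*1\*1/CC patient dosed as printed in mg/day would get 40–71% of the intended dose on days 2–6, and the most sensitive genotypes would get somewhat more than intended.

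The predicted-versus-actual outcome would be distorted directly. Bias in the two primary outcomes is possible but not quantified. The day-1 loading dose, the dosing rule from day 7 and the sample size are unaffected. The document does not show which version the clinic's calculator holds.

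**What to change.** 1. Check the line against the retrospective derivation of the algorithm. If it confirms a regression on the square root of weekly dose, change the exponent to 2 (equivalently, put the 0.5 on the dose), state mg/week and divide by 7 for the daily dose. If it shows exponent 1 in mg/day, print that instead.
2. Add one worked example per VKORC1 genotype. With exponent 2 at 70 y, 1.8 m², \*1\*1, CC, these would be 45.0, 32.1 and 21.0 mg/week for GG, AG and AA.
3. In the same check, reconcile the loading dose with the corrected maintenance dose.
4. Verify the calculator before any PGX dose is issued. If patients have already been dosed, document which version was used.
5. Preferably set a floor and a cap, since squaring gives 4.2 mg/week at 85 y/1.5 m² and 74.9 at 40 y/2.2 m².

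The cost is a protocol amendment for one corrected line with its unit and three examples, plus a calculator check. Design and sample size stay as they are.

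### The protocol tests baseline covariates for significance between randomised arms and describes no use of age, BSA and genotype in the outcome comparison; baseline description plus a prespecified adjusted model would be a cheap, modest gain in precision

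*Protocol*

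**What the plan says.** **Baseline.** In the Statistical analysis section, after an exploratory inspection that precedes inference, the protocol states: "Differences in potentially clinical covariates (e.g., Age, gender, BMI, BSA, etc.) will be assessed by" Student's t-test for continuous data and Fisher's exact test for frequencies. Age and BSA are named there. Genotype is not, and is covered at most by the closing 'etc.'.

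**Outcomes.** For primary and secondary endpoints, the same section says only that arms will be compared with suitable statistics depending on how the data are distributed. No covariate is named, and adjustment is neither planned nor ruled out. The section opens by promising that the analysis will be specified before any comparative analysis.

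**Available covariates.** Under Study procedures, genotyping of VKORC1, CYP2C9 and CYP4F2 "will be performed for each patients at the Department of Laboratory Medicine", so the data exist in both arms. Allocation is by block randomisation, with no stratification factor stated. The introduction says of the model built on age, BSA and these genotypes: "This algorithm could explain 55% of warfarin dose variability".

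**Sample size.** The calculation assumes "patients in control arm will experience a percentage of INR measures outside the therapeutic range will be 50" percent, a target of "10% of improvement in the percentage of INR out of range", an SD of 23%, "with a 80% of power" and "at a 5% significance level". With 15% drop-out it gives 100 per arm.

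**The concern.** Two matters are linked.

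First, randomisation makes the null hypothesis of a baseline test true by design. A small p-value shows only that chance has occurred. A large one does not show that an imbalance in a prognostic factor is harmless. Neither result should decide which covariates enter the outcome analysis. Yet the tests are placed ahead of inference while the form of the primary comparison is still open.

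Second, the trial's own rationale is that age, body size and genotype drive the dose a patient needs. Control patients all start on a uniform scheme, so these factors may plausibly predict early INR control. If they do, an unadjusted comparison leaves that variation in the error term, although it could be removed with data already in hand.

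What is at stake is some precision in the primary estimate, and clarity that any covariates were chosen in advance. The validity of the trial is not at stake.

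**Working it through.** **1. The plan's own figure.** Inputs from Sample size calculation and Statistical analysis: difference 10 percentage points, SD 23, two-sided alpha 0.05, power 80%, drop-out 15%.

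- n per arm = 2 × (1.960 + 0.842)² × 23² / 10² = 83.04, rounded up to 84 evaluable.
- With drop-out: 84 / 0.85 = 98.8, so 99 against 100 stated. It reproduces.
- Other readings do not fit: one-sided gives 66 evaluable; a relative 10% (5 points) gives 333 evaluable and 392 with drop-out; two proportions, 50% against 40%, gives 388.

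The stated size is therefore that of an unadjusted two-sample comparison of means. Evaluable patients at 100 randomised: 100 × 0.85 = 85 per arm. SE = 23 × √(2/85) = 3.53, and power is 80.5% (noncentral t).

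**2. Baseline tests.** If all nulls are true and the tests are independent, the chance of at least one p < 0.05 is 1 − 0.95⁴ = 18.5% for the four named covariates, and 1 − 0.95⁷ = 30.2% if the three genotypes are added. BMI and BSA are correlated, so the true figures are somewhat lower. The protocol does not say what would follow from such a result.

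**3. Possible gain from adjustment.** Let R² be the share of variance in the percentage of INRs out of range that the covariates explain. The document gives no value, so R² is an assumption. Residual SD = 23 × √(1 − R²); the CI narrows by 1 − √(1 − R²).

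| Assumed R² | Residual SD | SE (85 per arm) | Power | CI narrower by |
| --- | --- | --- | --- | --- |
| 0 | 23.0 | 3.53 | 80.5% | 0 |
| 0.05 | 22.4 | 3.44 | 82.4% | 2.5% |
| 0.10 | 21.8 | 3.35 | 84.4% | 5.1% |
| 0.20 | 20.6 | 3.16 | 88.3% | 10.6% |

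**4. Why 20% is optimistic.** Six scheduled INRs per patient (days 5, 7, 9, 12, 15, 19), taken as independent and each out of range with probability 0.5, give a within-patient SD of 100 × √(0.25/6) = 20.4. The share left for any patient-level covariate is then 1 − 20.4²/23² = 21%. If each patient's probability p varies with variance V, then (0.25 − V)/6 + V = 0.23² gives V = 0.0135, a share of 0.0135/0.0529 = 25%. An R² of 20% would thus need the covariates to capture 0.20/0.25 to 0.20/0.21, or roughly 80–94%, of all between-patient variation. Independence and a constant 50% are assumptions, so this ceiling is only indicative.

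**5. Price of the terms.** The table ignores the degrees of freedom spent. With VKORC1 (2), CYP2C9 (1), CYP4F2 at three levels (2), age (1) and BSA (1), k = 7. Chance imbalance then inflates the variance by about (N − 3)/(N − k − 3) = 167/160 = 1.044 at N = 170. Break-even is at R² of about 1 − 160/167 = 4%. Net power at R² of 0, 0.05, 0.10 and 0.20 is about 78.8%, 80.8%, 82.8% and 86.9%. The table therefore shows upper bounds, and the loss if the covariates explain nothing is under 2 points of power.

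**The case against.** The strongest case against is that nothing here is wrong. A comparison of randomised arms without covariates is unbiased, its standard error already allows for chance imbalance, and the planned size reaches 80% power without adjustment. A covariate model is commonly left to a statistical analysis plan, which is not at hand, and the protocol promises specification before comparative analysis. All of this stands. It is why the point is an improvement and not a fault.

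Several stronger readings are tempting, and the document does not support them:

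- *The covariates are used only for baseline tests.* They also set dosing in the pharmacogenetic arm, and they underlie the secondary outcome comparing predicted with actual maintenance dose. The baseline sentence does not name genotype.
- *Outcomes will be analysed without adjustment, or adjusted for whatever proves significant.* Neither is stated. No sentence links a baseline p-value to the outcome model. The order of steps leaves room for this and no more.
- *Since the covariates explain 55%, power could be far higher.* The 55% concerns dose. Putting it into the formula would give about 98.8% power, but for the wrong variable. The outcome counts INRs below 2 and above 3 alike, so patients at both ends of dose need can fail and linear terms may capture little. Genotype-guided dosing is meant to weaken the link in one arm, and INR-guided titration weakens it in both.

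The objection does not rescue the baseline tests. They are written into the protocol, and a later plan that added an adjusted model would not make them informative.

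**Conclusion.** The point holds as a low-cost improvement. The baseline significance tests are uninformative and should not guide the choice of covariates; removing them changes no result. The protocol describes the primary comparison only as a test chosen by data distribution, and it describes no use there of age, BSA and genotype data collected in both arms. The unadjusted analysis remains valid and the sample size is sound.

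The size of the gain rests wholly on an assumed R². For 0–10%, power at 85 per arm goes from about 80% to at most about 84%, with a CI at most about 5% narrower. Counting the seven model terms, the range is about 79% to 83%. For the reasons given against the 55% figure, the true value probably lies at the low end; 20% is an optimistic upper limit. The benefit that does not depend on R² is that the covariates are fixed before anyone has compared the arms.

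**What to change.** - Replace the baseline tests with a description by arm (means and SDs, medians and ranges, or counts), including the three genotypes, without p-values.
- Before any arm-level data are seen, prespecify a linear model for the percentage of INRs out of range, and likewise for TTR, on arm plus VKORC1 (three levels), CYP2C9 (any variant against none), CYP4F2, age and BSA. Report the adjusted mean difference with its 95% CI, and the unadjusted difference as a supporting analysis.
- State that no covariate will be added or dropped on the strength of an observed imbalance.

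Genotyping is done on Wednesday, while patients are enrolled and assigned from Monday, so genotype may not be known at allocation. Since genotype does not change with treatment, it is still a legitimate baseline covariate in the analysis.

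The cost is a few sentences and a few lines of code. No extra data and no change to the sample size are needed. Coding CYP4F2 in two groups instead of three would save one degree of freedom; either is acceptable if fixed in advance.
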